**Fig. 1 Fig1:**
[figure not shown]
Flow chart showing the design of the study (IHM = Individual Health Management; UC = Usual Care)

### Outcomes

The primary outcome measure to test the hypothesis of no differences between the effects of both intervention groups is change in body weight from baseline to month 12. Secondary outcome parameters are Body-Mass-Index, waist circumference, blood pressure, heart frequency, laboratory findings, and distribution of bodily fat measured by bio-impedance-analysis. The occurrence of adverse events will be captured systematically at each physical examination following the baseline testing. Weight reduction will also be analyzed by the frequency of responders in both groups. A responder at month 12 will be defined as a 7.5 % reduction of baseline body weight. The schedule for all examinations during the study is displayed in Table 1.

**Table 1 Tab1:** Study process chart

	Month				
Examination	0	3	6	9	12
Inclusion-/exclusion criteria^a^	X				
Informed consent^a^	X				
Randomisation	X				
Sociodemographic data	X				
Size	X				
Weight, waist circumference, blood pressure, heart frequency	X	X	X	X	X
Bio-Impedance-Analysis	X	X	X	X	X
Laboratory findings:					
Electrolytes (Ca, K, Cl, Mg, Na)	X				X
Liver enzymes (ASAT, ALAT, GGT, ALP, Bilirubin)	X				X
Kidney (Crea, Urea, Uric acid)	X				X
Blood count (Ery, Leuco, Ptl, Hk, Hb)	X				X
TSH (basal)	X				X
Fasten glucose	X	X			X
Trigycerides	X	X			X
Total cholesterol	X	X			X
HDL-/LDL-Cholesterol	X	X			X
Adverse events/effects		X	X	X	X

^a^to be checked before inclusion into study

### Statistical analysis

Based on indications from the literature we assumed a mean reduction for body weight after 12 months of 6 kg under IHM and of 3 kg under usual care conditions. Given a common standard deviation of 6 kg for the change in weight the sample size for the *t*-test for independent groups (α = 0.05, 2-sided, power 80 %) is estimated as 98 in one group and 49 in the second (allocation ratio 2:1). Hence, the total sample size is 150 participants.

The confirmatory analysis will be conducted using a 2-sided significance test at the 5 % significance level. Based on the intent-to-treat population the primary outcome (change in body weight Δ_month 0 – month 12_) will be tested by analysis of variance with the grouping factor ‘intervention’ controlled for baseline value. The factor ‘study centre’ will also be included to the test model. In participants with missing data for weight at month 12 (drop-outs) an adequate conservative imputation technique will be applied.

Secondary endpoints will be analyzed analogously but using an explanatory approach. Hence, a correction of the error probabilities due to multiple testing is not indicated. These analyses will be performed on both intent-to-treat and per-protocol populations. A responder analysis with respect to the primary outcome will be performed using a responder definition with a threshold of 7.5 % weight reduction at month 12 compared to the baseline value. Depending from the number of participants who chose the different nutritional regimen a subgroup analysis within the IHM group will be performed.

All captured data will be analyzed descriptively by appropriate statistical parameters: absolute and relative frequencies for categorical data and arithmetic means, medians, standard deviations for numerical data. Where indicated, 95 % confidence intervals will be presented.

Apart from the confirmatory analysis a series of sensitivity analyses will be performed to explore the impact of different factors on the results of the analyses. Relevant factors are among others adherence to the protocol, adherence to the intervention program IHM and different responder definitions.

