**Methods/Design:**

The study is a multicentre randomized controlled trial with observation duration of 12 months. Eight study centres are involved to include a minimal sample size of 150 participants. Randomization ratio is 2:1. Feasible persons are checked according to inclusion and exclusion criteria and after given informed consent are assigned randomly to one of two intervention programs: A) intervention group: comprehensive lifestyle modification program (Individual Health Management IHM) with 3 months reduction phase plus 9 months maintaining phase, B) control group: written information with advice for healthy food habits (Usual care UC). Participants of the IHM group have access to a web-based health portal and join 3 full-day and 10 two-hour training sessions during the first 3 months. During the remaining 9 months four refresh trainings will be performed. There are 3 different diet strategies (fasting, two-day diet, meal replacement) for free choice. Participants of the control group are provided with acknowledged rules for healthy food according to the German Nutrition Society (DGE). Examinations are conducted at baseline, after 3, 6, 9 and 12 months. They include body weight, waist circumference, blood pressure, laboratory findings and a bio-impedance analysis to measure body composition. Statistical analysis of the primary outcome ‘change of body weight after 12 months’ is based on ITT population including analysis of variance of the weight differences between month 0 and 12 with the factors ‘group’, ‘baseline value’ and ‘study centre’. Secondary outcomes will be analyzed exploratively.

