## Methods/Design

### Study design

The study is a multicentre randomized controlled trial. The study duration for each participant is 12 months with five sequential examinations. It will be performed in total in 8 study centres located in different spa towns all over Bavaria, and complemented by the outpatient unit of the Competence Centre for Complementary Medicine and Naturopathy at Klinikum rechts der Isar, Munich. The centres in the spas are affiliated to private practices of General practitioners. These centres are committed to be a part of the local core teams promoting Individual Health Management (IHM) which are pooled into a centrally coordinated network of health promotion called ‘IHM-Campus’.

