## Discussion

### Quality assurance and bias

The protocol was developed according to the Consort guidelines (see Additional files 1 and 2). All trial physicians are qualified regarding the legal requirements according the German Drug Law (AMG) and in line with the guidelines for GCP and ICH. Staff members of the study centres at the participating spas being involved in coaching of the IHM group members are trained and certified as health coaches.

The study will be monitored by a professional institution with acknowledged expertise in supervision of clinical trials of all kinds (Munich Study Centre at the Medical faculty of TUM). The monitoring plan comprises a central indoor-monitoring as well as onsite visits at the participating study centres. The confirmatory analysis of the data is conceptualized and will be performed by an independent statistician at the institute for medical statistics and epidemiology at the TUM.

Although randomization should eliminate selection bias there are some other issues with potential impact on the conclusiveness of the study. First, we tried to avoid early drop-outs by comprehensive information of the study. Both intervention arms are introduced as strategies to reduce body weight, and the acceptance was enhanced by choosing a 2:1 allocation ratio assuming the IHM group as the more popular one. Participants allocated to the IHM group will have a free choice of different dietary strategies. So for example, if someone does not wish to do fasting, this is not to discourage him from participating in the study since there are other options for an individual dietary strategy.

Another issue is loss to follow-up which may lead to biased estimates of intervention effects. While during the first three months the high frequency of personal meetings in the IHM group warrants a close relationship between the study coaches and the participants there is more need for careful following up the members of the comparison group. We will remind them of the upcoming examination visits by phone or mail and consider the individual requirements to arrange feasible dates. We will implement procedures to minimize the number of drop-outs, and we will ask to tell us the reasons for withdrawal, where possible. Nevertheless we anticipate an attrition rate of about 10 %, and appropriate methods for handling these drop-outs in the statistical analysis will be applied (see ‘Statistical analysis’).

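### The 80% power at 150 participants leaves out the protocol's own 10% attrition; with month-12 weights from about 135, power is about 78%

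*Protocol article*

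**What the plan says.** All references are to the protocol article.

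- **Statistical analysis, planning assumptions.** The assumed effect is a "mean reduction for body weight after 12 months of 6 kg under IHM and of 3 kg under usual care conditions". The spread is given as follows: "Given a common standard deviation of 6 kg for the change in weight". The test is a t-test for independent groups with "α = 0.05, 2-sided, power 80" per cent.
- **Statistical analysis, resulting size.** It "is estimated as 98 in one group and 49 in the second (allocation ratio 2:1). Hence, the total sample size is 150 participants".
- **Abstract, Methods/Design.** "Eight study centres are involved to include a minimal sample size of 150 participants". So 150 is the number to be included, not the number expected to complete.
- **Discussion, Quality assurance and bias.** "Nevertheless we anticipate an attrition rate of about 10" per cent. The same sentence refers the reader to the Statistical analysis section for the handling of drop-outs.
- **Statistical analysis, missing data.** "In participants with missing data for weight at month 12 (drop-outs) an adequate conservative imputation technique will be applied". The technique is not named. The primary analysis is by intention to treat and adjusts for baseline weight and study centre.

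**The concern.** A t-test sample size counts participants whose outcome is known, here those with a weight at month 12. The protocol reaches 147 on that basis, rounds it up to 150, and makes 150 the recruitment figure. Elsewhere it expects to lose about one participant in ten over the 12 months. The two statements do not fit together: the quoted power needs nearly complete follow-up, which the protocol says it does not expect.

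The trial has one confirmatory test. If it gives a null result, readers will judge that result against a power of 80%, which is somewhat more than the protocol's own assumptions support.

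**Working it through.** **Inputs, all from the protocol article.** Difference δ = 6 − 3 = 3 kg; common SD σ = 6 kg; two-sided α = 0.05; target power 80%; allocation 2:1; 98 + 49 = 147, set at 150; attrition about 10%.

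**Step 1: reproduce the stated size.** With the normal approximation and 2:1 allocation, the smaller group needs

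n = (1.960 + 0.842)² × σ² × (1 + 1/2) / δ² = 7.849 × 36 × 1.5 / 9 = 47.1, rounded up to 48.

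That gives 96 + 48 = 144. The exact non-central t calculation also gives 96 + 48 as the smallest 2:1 size (80.2%). The stated 98 + 49 is within 3 participants of this and slightly generous, so the figure reproduces.

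**Step 2: the allowance contained in 150.** 150 − 147 = 3, and 3/150 = 2%.

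**Step 3: power at different numbers of observed month-12 weights.** The standard error is SE = 6 × √(1/n₁ + 1/n₂), the non-centrality is 3/SE, and df = n₁ + n₂ − 2.

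| Month-12 weights (IHM / UC) | SE (kg) | Non-centrality | Power |
|---|---|---|---|
| 98 / 49 | 1.050 | 2.858 | 81.0% |
| 100 / 50 (no loss) | 1.039 | 2.887 | 81.8% |
| 96 / 48 (4% loss) | 1.061 | 2.828 | 80.2% |
| 95 / 47.5 (5% loss) | 1.066 | 2.814 | 79.8% |
| 90 / 45 (10% loss) | 1.095 | 2.739 | **77.6%** |

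The normal approximation gives 78.2% at 90/45. Power crosses 80% between 4% and 5% loss, about half of what the protocol expects.

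**Step 4: uneven loss of the same 15 participants.** Power is 78.5% at 88/47, 76.6% at 92/43 and 75.0% at 95/40. Loss from the smaller usual-care arm costs more. The Discussion says that this arm needs the more careful follow-up.

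**Step 5: size needed to keep the calculated number observed.** 147/0.9 = 163.3, so 164 randomised. From the minimum of 144, 144/0.9 = 160.

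**Step 6: two features of the planned analysis that the t-test leaves out.** Both need assumptions that the protocol does not state.

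- *Imputation.* As an illustration, assume that 10% of each arm drops out and is given zero change, and that 6 kg and 3 kg are the effects in those who stay. The means become 5.4 and 2.7 kg, a difference of 2.7 kg. The variances are 0.9 × 36 + 0.09 × 36 = 35.64 and 0.9 × 36 + 0.09 × 9 = 33.21, with pooled SD 5.90 kg. With 100/50, power is 74.7%.
- *Baseline adjustment.* A correlation ρ between baseline weight and weight change reduces the SD to 6 × √(1 − ρ²). At 90/45, with 9 degrees of freedom taken off for the covariates, power is 78.0%, 79.2%, 80.1% and 81.3% for ρ = 0.1, 0.2, 0.25 and 0.3. A ρ of about 0.25 would be needed to regain 80%.

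**The case against.** The strongest reply is that the confirmatory analysis is not the test used above. It is by intention to treat with missing weights imputed, so all 150 participants enter it, and it adjusts for baseline and centre. The Discussion sends the 10% to the analysis section, so attrition is not ignored. In addition, 150 is called a minimum, and a gap of 2.4 points is small beside the uncertainty in the planning values: at 90/45, an SD of 5.8 kg gives 80.3% and one of 6.5 kg gives 70.9%.

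Much of this stands, and it limits the point.

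- A reader might infer that the primary analysis will rest on 135 participants. It will not: 135 is the number expected to have an observed month-12 weight.
- A reader might also infer that imputation is bound to dilute the effect, so that power is about 75%. The protocol does not support that as fact. It names no technique, weights at months 3, 6 and 9 are available to inform an imputation, and the assumed 6 kg and 3 kg come from literature that may already include drop-outs. The 74.7% is an illustration only.

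The reply does not restore the stated 80%. Filling in missing weights keeps the head count at 150 but adds no real information. Baseline adjustment may recover some power, but the protocol gives no correlation and does not offer adjustment as an offset. Calling 150 a minimum sets no higher target; the Statistical analysis section gives 150 as the total.

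**Conclusion.** The point holds as a modest one that should be fixed. On the protocol's own effect, SD, test and attrition rate, 150 randomised gives about 78% power (77.6%), not 80%. The result assumes equal proportional loss in the two arms and the unadjusted t-test that the protocol used for planning. Uneven loss of the same size gives 75.0% to 78.5% in the splits tried.

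Two stronger readings are not supported. The sample-size calculation is not wrong in itself: 98 + 49 reproduces and is slightly generous for complete data. What is missing is an allowance that the protocol's own attrition figure calls for. Nor is the confirmatory test undermined, since its type I error and the quantity it estimates are unaffected. It is also not shown that the adjusted analysis must fall short of 80%, because that depends on a correlation the protocol does not give.

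**What to change.** In the Statistical analysis section, say that 147 is the number of participants with a month-12 weight that the t-test calls for. Add that 150 randomised with the anticipated 10% attrition gives about 78% power by that test. A short note can follow: a conservative imputation may lower this figure and baseline adjustment may raise it. If either effect is quantified, the imputation method or the assumed correlation should be stated with it.

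The cost is a sentence or two and a slightly less favourable stated power, with no extra participants and no change of design. If the sponsor prefers to keep the calculated 147 observed, the alternative is to randomise about 164, which is 14 more than planned.

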### Ethical review

Ethical approval for this study was obtained from the ethical review board of the Medical faculty of TU Munich (file number 97/14). The investigators will ensure that the study will be conducted in compliance with the ethical guidelines as set out by this committee, and in line with the guidelines for good clinical practice (GCP).

## Discussion

### Quality assurance and bias

The protocol was developed according to the Consort guidelines (see Additional files 1 and 2). All trial physicians are qualified regarding the legal requirements according the German Drug Law (AMG) and in line with the guidelines for GCP and ICH. Staff members of the study centres at the participating spas being involved in coaching of the IHM group members are trained and certified as health coaches.

The study will be monitored by a professional institution with acknowledged expertise in supervision of clinical trials of all kinds (Munich Study Centre at the Medical faculty of TUM). The monitoring plan comprises a central indoor-monitoring as well as onsite visits at the participating study centres. The confirmatory analysis of the data is conceptualized and will be performed by an independent statistician at the institute for medical statistics and epidemiology at the TUM.

Although randomization should eliminate selection bias there are some other issues with potential impact on the conclusiveness of the study. First, we tried to avoid early drop-outs by comprehensive information of the study. Both intervention arms are introduced as strategies to reduce body weight, and the acceptance was enhanced by choosing a 2:1 allocation ratio assuming the IHM group as the more popular one. Participants allocated to the IHM group will have a free choice of different dietary strategies. So for example, if someone does not wish to do fasting, this is not to discourage him from participating in the study since there are other options for an individual dietary strategy.

Another issue is loss to follow-up which may lead to biased estimates of intervention effects. While during the first three months the high frequency of personal meetings in the IHM group warrants a close relationship between the study coaches and the participants there is more need for careful following up the members of the comparison group. We will remind them of the upcoming examination visits by phone or mail and consider the individual requirements to arrange feasible dates. We will implement procedures to minimize the number of drop-outs, and we will ask to tell us the reasons for withdrawal, where possible. Nevertheless we anticipate an attrition rate of about 10 %, and appropriate methods for handling these drop-outs in the statistical analysis will be applied (see ‘Statistical analysis’).

The potential effectiveness of an intervention is affected by non-adherence to the intervention program. The IHM program under investigation is requesting a high level of active participation. During the whole study there are sixteen personal meetings scheduled. Before enrollment to the study all potential study participants are informed in detail on the requirements. Although basically accepted it has to be anticipated that especially for those participants with a longer distance between their domicile and the study centre not all appointments will be kept. We will implement a simple score for compliance based on the rate of participation and will use this for sensitivity analyses to check for potential association with effect sizes.

Although the process of IHM is clearly predefined a broad range of individual health behavior actually practiced in the participants’ everyday life has to be anticipated. This variety of options is due to the individually different life situations and thus will not automatically lead to an exclusion from the program or the analysis of the trial. Similarly, participants of the UC group who apparently improve their lifestyle only by written advice need not be excluded.

### Expected benefit

This randomized study will contribute to the evidence of a comprehensive lifestyle program which in the current form has not yet been proved. The program with an active duration of 12 months promises to achieve sustainable effects in weight reduction. Based on a blended learning concept and using web-based e-health tools the program might overcome the well-known experience of many diet programs. Although knowing how lifestyle should be modified it proves to be hard to sustainably make an improved health related behavior reality in everyday life. Furthermore, the multicentre study will show whether comprehensive lifestyle training can be implemented successfully in local health and prophylaxis centres at various spas.

## Abbreviations

AMG: Arzneimittelgesetz, German pharmaceutical products act
BMI: Body-Mass-Index
BP: Blood pressure
CVD: Cardiovascular disease
DGE: Deutsche Gesellschaft für Ernährung
GCP: Good clinical practice
ICH: International conference on harmonisation of technical requirements for registration of pharmaceuticals for human use
IHM: Individual health management
GP: General practitioner
RCT: Randomized controlled trial
TUM: Technische Universität München
UC: Usual care
